### Secondary outcomes

The following indicators will be used to comprehensively assess anatomical outcome: (1) type I closure rate of MH 3 months after operation; (2) type II closure rate of MH 6 months after operation; and (3) type II closure rate of MH 3 months after operation.

Functional outcomes will be assessed as follows: (1) changes in BCVA 3 and 6 months after operation compared with baseline; (2) changes in P1 wave response density in the macular region 3 and 6 months after operation compared with baseline; and (3) changes in macular retinal sensitivity 3 and 6 months after operation compared with baseline.

Furthermore, the number of adverse events and reactions, abnormality of ophthalmic examination, abnormal systemic symptoms and laboratory results will be recorded at each follow-up visit.

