### Sample size

Although no RCT of lens capsule flap transplantation in the treatment of HMMHRD has been reported, according to the existing published papers^23 29^ related to this study, the type I closure rate in the experimental group was expected to be 96.0%, whereas the rate in the control group was should be 65.0%. An a priori power analysis conducted using a two-tailed test (power=0.8) at the 5% significance level indicated that 21 participants are required in each group. Considering the attrition rate of 20%, the sample size in each group was determined as 27. With the 1:1 allocation, 54 participants will be recruited.

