### Statistical analysis

SPSS (V.22.0; SPSS, Inc) and GraphPad Prism (V.8, GraphPad software Inc, San Diego, California, USA) will be used for data processing and analyses. Categorical variables will be expressed as numbers and frequencies, and between-group differences will be evaluated with Fisher’s exact test. Continuous variables will be expressed as the mean±SD. The Kolmogorov-Smirnov test will be used to determine whether continuous variables are normally distributed. The Student’s t-test will be used for normally distributed data, and the Wilcoxon signed-rank test will be used for non-normally distributed data. All statistical tests will be two-sided with p<0.05 considered statistically significant.

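### The stated tests take months 3 and 6 separately, so an eye missing at month 6 adds nothing to the month-6 functional comparison, which can be biased if poorly performing eyes are the ones lost

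*Protocol article*

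**What the plan says.** Under Secondary outcomes, the Protocol article lists three functional measures, each at two post-operative visits: "changes in BCVA 3 and 6 months after operation compared with baseline", "changes in P1 wave response density in the macular region 3 and 6 months after operation compared with baseline" and "changes in macular retinal sensitivity 3 and 6 months after operation compared with baseline". Table 1 schedules mfERG and MP-1 microperimetry at screening, month 3 and month 6, and BCVA at every visit.

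Under Statistical analysis, the methods for continuous variables are a normality check followed by one of two tests: Student's "t-test will be used for normally distributed data, and the Wilcoxon signed-rank test will be used for non-normally distributed data". The section gives no model that handles two visits together and no rule for missing values.

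Under Sample size, loss is anticipated: "Considering the attrition rate of 20%, the sample size in each group was determined as 27".

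The Withdrawal criteria include loss to follow-up, new eye disease, a need for other eye treatment, safety concerns, and unsuitability of the treatment (remedial treatment included). The section on safety and adverse events also withdraws participants who have a severe adverse event.

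**The concern.** A t-test of month-6 change uses only eyes with a month-6 value. Without imputation, the eyes lost between months 3 and 6 drop out of that comparison although their month-3 result is known and is likely to be correlated with the missing one. The result is unbiased if loss is unrelated to how the eye was doing. That is doubtful here, because several withdrawal rules tend to remove eyes that are doing badly.

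The loss may also be unequal between arms. The Overview hypothesises better functional recovery with the capsule flap, and the Sample size section expects far more closure failures in the control arm. If poor control eyes leave, those that remain look better than the arm really is, and the functional difference at month 6 shrinks. The trial would then understate the effect that it set out to show.

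A second defect sits in the same sentence. The test named for non-normal data, "the Wilcoxon signed-rank test will be used for non-normally distributed data", is for paired observations. Applied to before-and-after values within an arm, it gives no comparison between arms.

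**Working it through.** **Step 1: the plan's own figures.** With closure 0.96 v 0.65, two-sided 5% and power 0.80, the arcsine formula n = 2(z₀.₉₇₅ + z₀.₈₀)²/h², where h = 2·asin√0.96 − 2·asin√0.65, gives 21.06 per arm. The unpooled normal formula gives 21.7. The stated 21 is thus reproduced. Inflation for 20% attrition: 21/0.8 = 26.25, rounded up to 27, as stated. The plan gives no power for the functional outcomes.

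**Step 2: eyes at month 6.** 27 × 0.8 = 21.6 per arm, so 27 − 21.6 = 5.4, or about 5 to 6 eyes per arm missing.

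**Step 3: why loss may differ by arm.** Expected eyes without type I closure are 27 × 0.04 ≈ 1.1 in the experimental arm and 27 × 0.35 ≈ 9.5 in the control arm. If such eyes more often need further treatment, the withdrawal rules act mainly on the control arm.

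**Step 4: form of the bias.** Take month-3 and month-6 outcomes as bivariate normal with SD 1 and correlation ρ, and let loss depend on the month-3 value. The mean at month 6 among completers in an arm is then μ₆ + ρ × (completers' month-3 mean − μ₃). The bias in the arm difference is ρ × (shift in experimental arm − shift in control arm). It is zero if the two shifts are equal.

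**Step 5: size.** The documents give no functional effect, no correlation and no loss mechanism. The following are assumptions: 27 per arm, true effect 0.8 SD, 20% lost overall, the same loss rule in both arms, ρ from 0.5 to 0.8. The joint estimate is the likelihood estimate that uses month-3 values.

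| Odds ratio of loss per SD worse at month 3 | Completer estimate (SD) | Joint estimate, all lost eyes seen at month 3 |
|---|---|---|
| 1 (random) | about 0.80 | about 0.80 |
| 1.6 | about 0.77–0.80 | about 0.80 |
| 2.7–7.4 | about 0.65–0.76 | about 0.80 |

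Shortfall in the last row: (0.80 − 0.76)/0.80 = 5% to (0.80 − 0.65)/0.80 ≈ 19%. A separate run gave 0.64–0.75, that is 6–20%. Hence about 5–20%.

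**Step 6: check on the formula.** In another run, with odds ratio e^1.5 ≈ 4.5 and 22–23% lost, the bias was −0.078, −0.108 and −0.145 SD at ρ = 0.5, 0.7 and 0.9. Dividing by ρ gives −0.156, −0.154 and −0.161, close to constant as Step 4 requires. With no true effect and the same rule in both arms, bias was about zero.

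**Step 7: stress case.** If poor eyes leave mainly from the control arm, the bias was −0.26 to −0.58 SD. Total loss in that scenario was 23–29%, above the planned 20%, so it marks an extreme and is not the headline figure.

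**Step 8: limits of joint modelling.** If half of the lost eyes were already gone before month 3, the joint estimate is about 0.74–0.78 at odds ratios 2.7–7.4, so only part of the bias is removed. Under random loss, the standard error falls by only about 1–7%.

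**The case against.** The strongest reply is that this is a condensed article. Analysis sets and missing-data rules are commonly left to a full protocol or analysis plan, and nothing here excludes a mixed model. That stands as far as it goes: silence on imputation is not the finding. The article does, however, name its tests for continuous outcomes, and those tests fit a design with two post-operative visits and expected loss poorly.

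Some stronger readings should be resisted.

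- A reader might infer that the plan restricts analysis to completers. It states no analysis set; exclusion at month 6 follows from the named tests only if nothing is imputed.
- A reader might infer that month-3 data of lost eyes are thrown away. Month 3 is itself an outcome time, so those values can enter the month-3 comparison; they are merely unused at month 6. Whether withdrawn participants are removed from all analyses is not stated.
- A reader might infer that bias is certain. It is conditional on outcome-related loss that shifts the arms differently.

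It is also fair to say that the 20% is a sample-size allowance and no forecast of loss after month 3, that training to promote retention is planned, and that these are secondary outcomes. In the scenarios with a common loss rule the error is towards no difference, so it would not create a false benefit. The month-6 closure comparison by Fisher's exact test is a separate matter.

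**Conclusion.** The point holds in conditional form. As worded, the tests leave month-3 information unused at month 6, and the trial's own withdrawal rules make outcome-related loss plausible. The month-6 functional differences can therefore be biased: about 5–20% too small for an assumed 0.8 SD effect and odds ratios of 2.7–7.4 per SD, little at 1.6, and near zero if loss is random. Precision is a minor argument; possible bias is the reason to act. These sizes rest on the assumed effect, correlation and loss mechanism. That the signed-rank test does not compare independent arms needs no assumption. The change should be made before analysis, as an improvement to secondary analyses and not as a threat to the primary result.

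**What to change.** In Statistical analysis, replace the separate tests for the functional outcomes with one mixed model for repeated measures per outcome:

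- **Response:** month-3 and month-6 values; for BCVA the month-1 value may enter too.
- **Terms:** baseline value, hole-size stratum (400 µm), arm, visit and arm-by-visit, with unstructured covariance.
- **Eyes:** every randomised eye with at least one post-operative value among the modelled visits.
- **Result:** the month-6 arm difference with 95% CI.
- **Assumption:** state that data are taken as missing at random.
- **Skewed data:** a rank-based two-sample test as sensitivity analysis, in place of the signed-rank test.

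The cost is analysis wording only. Table 1 already collects the data, and SPSS, the stated software, has a mixed-model procedure. The downsides are small: the model assumes approximate normality, does not cover loss driven by unseen month-6 status, and recovers little for eyes lost before month 3. No imputation of closure grades is proposed here; with 96% closure expected in one arm, about one failure in 27 eyes, such a model would be unstable.

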### Data management and safety monitoring board

Basic demographic information and data on history of ocular diseases will be collected preintervention. All the data in this study will be collected from the clinical information system of our hospital and recorded in the case report format (CRF) in electric data collection system developed by Shanghai General Hospital. Every participant included will be distinguished with a study identifier and initial without full name. An electronic password-protected document containing all the information from the CRFs will be set up for statistical analysis. Relevant documents will be stored at the Department of Ophthalmology of Shanghai General Hospital after the study. The confidentiality and safety of participants’ data are guaranteed. All the data will be reserved for 5 years for the purpose of the designated scientific study.

To ensure the integrity of the RCT and protect the rights and health of the participants, a Data and Safety Monitoring Board will be constituted. As an independent advisory group, it will ensure the scientific integrity and ethical standards of the RCT and be responsible for data evaluation during the study period. The Data and Safety Monitoring Board will be developed in accordance with the Operational Guidelines for the Establishment and Functioning of Data and Safety Monitoring Boards of the WHO. Researchers will be trained to collect good quality data, promote participant retention and complete follow-up. Data analysts will be trained on data entry, coding, security and storage. Statisticians will provide training on data assessment and statistical analysis.

### Safety and combined operation-related adverse events

Possible phacoemulsification and intraocular lens implantation combined with vitrectomy complications include intraocular haemorrhage, suprachoroidal haemorrhage, endophthalmitis, uveitis, intraocular lens dislocation and corneal endothelial decompensation. Lens capsule flap transplantation may increase the risk of rejection, although the capsule flap will be immersed in sterile distilled water for 30 min. However, to date, no adverse reactions caused by lens capsule flap transplantation for the treatment of MH have been reported. During the trial, we will record and analyse any surgery-related adverse events (including the type and number) in each group and possible causes. Patients will receive appropriate intervention for any adverse events that occur during the treatment and follow-up phases. Severe adverse events will be reported immediately to the primary investigator, and affected participants will be withdrawn from the study.

### Patients and public involvement

Neither the patients nor the public will be involved in the design of the study, nor will they be involved in its conduct (including outcome measurements). No attempt will be made to assess the burden of the intervention on the patients by themselves. Results excluding personal data will be made available on request.

### Sample size

Although no RCT of lens capsule flap transplantation in the treatment of HMMHRD has been reported, according to the existing published papers^23 29^ related to this study, the type I closure rate in the experimental group was expected to be 96.0%, whereas the rate in the control group was should be 65.0%. An a priori power analysis conducted using a two-tailed test (power=0.8) at the 5% significance level indicated that 21 participants are required in each group. Considering the attrition rate of 20%, the sample size in each group was determined as 27. With the 1:1 allocation, 54 participants will be recruited.

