In 2019, Grewal *et al*^21^ first reported that the lens capsule was transplanted to the MH for the treatment of refractory MH. Peng *et al*^22 23^ used an autologous or allogeneic lens capsule to treat refractory MH. The healing rate can reach 90% and 96%, and the visual acuity of patients can be improved. Similar to the ILM, the lens capsule is a kind of basement membrane. Although the lens capsule is thicker than the ILM, it is quite flexible. Therefore, positioning the lens capsule at a designated place in the retina is easier than the ILM. For most patients who need surgery for HMMHRD, the degree of lens turbidity reaches the surgical indication of cataract phacoemulsification. Therefore, most doctors will choose to complete the operation together with cataract surgery to easily obtain the capsule tissue. The mechanism of lens capsule transplantation in the treatment of MH is similar to that of ILM. The lens capsule can be used as a scaffold to promote the proliferation and migration of Müller cells in the retina and promote the healing of MHs. The study found that the lens capsule as a stent still existed and did not become thinner after nearly 3 years of follow-up.^23^ Appropriate size and reasonable placement of lens capsule graft is the key to successful surgery.^23^ Mastery of certain surgical skills is necessary to fill the lens capsule at the MH. Moreover, lens capsule transplantation cannot only promote the healing of MH but also improve the vision of patients.^20 24 25^ In addition, lens epithelial cells on the anterior capsule flap can be removed using distilled water, resulting in low antigenicity.^23^ In the actual operation of capsule transplantation, Chen *et al*^16 20^ reported that the lens capsule is easier to process and insert MH than ILM, making it possible to vigorously promote this technology.

Based on the advantages of easy access, easy operation of lens capsule, combined with the clinical prognosis of high retinal reattachment rate and better improvement of visual function found in the capsule transplantation group in the previous study, our team plans to conduct a prospective randomised controlled trial of vitrectomy combined with lens capsule flap transplantation in the treatment of HMMHRD to explore the efficacy and safety of this operation in retinal reattachment and functional recovery after the treatment of HMMHRD.

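### Under the planned Fisher's exact test the stated power of 0.8 is about 68% with 21 evaluable patients per group and about 76% with 27, and it rests on a 96% rate whose endpoint and population are not explained

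*Protocol article*

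**What the plan says.** The Sample size section of the protocol article draws its planning rates from earlier reports, "according to the existing published papers^23 29^ related to this study". It states that "the type I closure rate in the experimental group was expected to be 96.0"% and that "the rate in the control group was should be 65.0"%. The power analysis was "conducted using a two-tailed test (power=0.8) at the 5% significance level", and it "indicated that 21 participants are required in each group". Attrition is then added: "Considering the attrition rate of 20%, the sample size in each group was determined as 27", which makes 54 in total.

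The Abstract and the Statistical analysis section both assign the comparison of type I closure to Fisher's exact test, two-sided, at p<0.05.

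The Introduction describes the earlier lens capsule work, references 22 and 23, as studies that "used an autologous or allogeneic lens capsule to treat refractory MH" and reports: "The healing rate can reach 90% and 96"%. The Anatomical measurement section defines type I and type II closure as separate categories. Only type I closure, at 6 months, is the primary outcome.

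**The concern.** Two features of the sample-size statement call for a check.

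First, it gives no formula, and 21 per group is small for a comparison that will use Fisher's exact test. That test is conservative in small samples. If 21 came from a large-sample or transformation formula, the power of the planned test would be lower than stated.

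Second, the same figure of 96% appears in two places under different names and for different patients: a healing rate in refractory macular hole in the Introduction, and a type I closure rate in macular hole with retinal detachment in the Sample size section. Reference 23 is cited in both. The Introduction also gives a second figure, 90%. If healing included some type II closures, or if the rate did not carry over to this population, the true type I rate could be below 96%.

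At stake is how the result is read. Someone who believes the power is 0.8 will take a non-significant result as fairly strong evidence against a large benefit. With much lower power, that inference is unsafe.

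**Working it through.** **Inputs**
- Experimental rate 96.0%, control rate 65.0%, two-sided 5%, power 0.8, 21 per group, 20% attrition, 27 per group (Sample size).
- Planned test: two-sided Fisher's exact test, significant if p<0.05 (Abstract; Statistical analysis).
- Alternative experimental rate: 90% (Introduction).

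**Step 1. Reproduce the plan's figure.** The arcsine formula is n = 2(1.960 + 0.842)² / h², with h = 2·arcsin√0.96 − 2·arcsin√0.65.
- h = 2.7389 − 1.8755 = 0.8634
- n = 2 × 7.849 / 0.7454 = 21.06 per group; at exactly 21 the arcsine power is 0.799
- The unpooled normal formula gives 7.849 × (0.96×0.04 + 0.65×0.35) / 0.31² = 21.7, so 22.
- Attrition: 21 / 0.80 = 26.25, so 27 per group and 54 in total.

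The plan's 21, 27 and 54 are therefore reproduced by approximate formulas. The formula actually used is not stated, so arcsine is an inference from the match.

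**Step 2. Power of the planned test at the plan's own rates.** With n per group, power is the sum, over all pairs (x, y) for which Fisher's two-sided p is below 0.05, of Bin(x; n, p₁) × Bin(y; n, p₂). Here p₁ is the experimental rate and p₂ = 0.65.

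| Experimental rate | 21 per group | 27 per group |
|---|---|---|
| 96% | 0.676 | 0.765 |
| 93% (midpoint; an assumption) | 0.517 | 0.615 |
| 90% | 0.383 | 0.473 |

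(The 0.765 is 0.7645 before rounding, hence about 76%.) The 27-per-group column needs complete follow-up. The 21-per-group column is roughly what the planned attrition leaves, since 27 × 0.80 = 21.6.

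**Step 3. How far short the plan falls.** Searching upward from 20 per group, Fisher power first reaches 0.8 at 29 evaluable per group for 96% v 65%, and at 49 for 90% v 65%. These numbers gauge the gap; they are not proposed sample sizes.

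**Step 4. Separate the two causes at 21 per group.**
- Choice of test: from 0.80 (stated) to 0.68 at 96%.
- Choice of rate: from 0.68 to 0.38 on moving from 96% to 90% under Fisher's test.
- For comparison, the arcsine approximation at 90% gives 0.52 (21 per group) and 0.63 (27 per group). Power below one half at 90% is therefore a statement about Fisher's test, not about every test.

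**The case against.** The strongest reply is that the arithmetic is sound and the source of the 96% cannot be inspected. Both are true. The figures 21, 27 and 54 follow from the stated rates by a recognised formula, and that is not disputed. The gap lies between that formula and the test the protocol names.

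A reader might infer more than the document supports.
- *That the 96% is mislabelled.* The Introduction does not define healing. The definitions of type I and type II closure are this trial's own, not those of the cited series. Reference 23 may have reported type I closure, in which case both labels are correct. Linking the 96% to reference 23 is itself an inference from the order of figures and citations.
- *That the more favourable figure was selected.* The Introduction also credits reference 23 with the distilled-water preparation and with the point on graft size and placement, and the Experimental group section uses that preparation and specifies size and placement. That is a possible technical reason for planning from that source.
- *That 90% is the autologous result and so the one matching this trial's flap.* Only word order suggests this.
- *That the 0.8 holds at 96% and fails only at lower rates.* Under the planned test it fails at 96% as well.

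The direction of any population difference is also open. The low closure rate mentioned in the Introduction concerns simple vitrectomy, which neither arm receives, and the eligibility criteria exclude several adverse features.

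A further objection is that the sensitivity check moves only the experimental rate. With assumed lower control rates, Fisher power at 90% is 52% and 63% (control 60%) or 65% and 77% (control 55%) for 21 and 27 per group. This stands: the 38% to 47% range depends on the plan's own 65%. It does not affect the shortfall at 96% v 65%, which uses the plan's figures unchanged.

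Finally, the section does acknowledge that no randomised trial in this condition has been reported, and it calls the rate an expectation. That candour does not correct the stated power.

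**Conclusion.** The point holds in two parts of unequal strength.

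The firm part is numerical. At the plan's own rates, alpha and sample size, the test it names has power of about 68% with 21 evaluable patients per group and about 76% with 27, not 80%. The only assumptions are independent binomial outcomes and an unstratified two-sided Fisher's exact test, as described.

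The second part is a gap in explanation, not a demonstrated error. The 96% changes name and population between the Introduction and the Sample size section, and nothing links the two. It matters because power is very sensitive to this rate: at 90%, with control at 65%, it is about 38% to 47%. The document does not establish that the true rate is below 96%.

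**What to change.** In the Sample size section:
1. Restate power under the two-sided Fisher's exact test against 65%, for 21 and 27 evaluable patients per group: about 68% and 76% at 96%, and, as a sensitivity value, about 38% and 47% at 90%.
2. State whether the source's 96% counts type I closure only and in which population it was observed. If it is not type I only, describe it as an optimistic assumption. The authors should check the source before rewording, since relabelling it as a healing rate without checking could introduce an error.
3. Give the reason for applying the rate to macular hole with retinal detachment in high myopia.

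This takes a few sentences. It adds no patients and leaves the test, the endpoint and the conduct of the trial unchanged. The cost is a less favourable stated power.

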**Methods and analysis:**

This single-centre, single-blind, prospective, randomised clinical trial will include 54 patients with HMMHRD who will first undergo phacoemulsification and intraocular lens implantation and then vitrectomy combined with lens capsule flap transplantation (experimental group) or ILM tamponade (control group). Study participants will be randomly allocated in a 1:1 ratio to experimental and control groups. Follow-up will be conducted 1, 3 and 7 days and 1, 3 and 6 months after surgery in both groups. Necessary examinations will be performed at each follow-up visit. Measurement outcomes include postoperative situation of macular hole closure, best-corrected visual acuity, macular retinal function and macular retinal sensitivity. The primary outcome is type I closure rate of MH 6 months after operation. Intergroup comparisons of the proportions of patients with type I closure of MH will be performed with Fisher’s exact test.

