### Primary outcome

The primary outcome is type I closure rate of MH 6 months after operation.

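### The stated 80% power at 21 per group does not hold for the Fisher's exact test that the protocol names: power is about 68%, and about 76% even if all 54 participants are evaluable

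*Protocol article*

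**What the plan says.** The primary outcome is binary: "The primary outcome is type I closure rate of MH 6 months after operation" (Primary outcome).

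The Sample size section gives the planning rates: "the type I closure rate in the experimental group was expected to be 96.0" per cent, and "the rate in the control group was should be 65.0" per cent. It then states that a "power analysis conducted using a two-tailed test (power=0.8) at the 5% significance level indicated that 21 participants are required in each group". Attrition comes next: "Considering the attrition rate of 20%, the sample size in each group was determined as 27", which makes 54 in total at 1:1 allocation. The section does not name the test or formula behind the 21.

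The analysis test is named in two places. In the Abstract (Methods and analysis), comparison of the proportions with "type I closure of MH will be performed with Fisher’s exact test". In Statistical analysis, for categorical variables, "between-group differences will be evaluated with Fisher’s exact test". That section makes all tests two-sided at p<0.05.

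**The concern.** A trial's power is the power of the test it will use. Someone who reads the Sample size and Statistical analysis sections together will take it that Fisher's exact test has 80% power with 21 evaluable participants per group. Fisher's test is conservative in small samples, because its attainable type I error lies well below the nominal 5%. A size taken from a large-sample formula can therefore fall short of its target.

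What is at stake is the chance of missing the planned effect on the primary outcome. The protocol implies one in five. If the true figure is nearer one in three, the ethics committee, the monitoring board and later readers are working from the wrong number.

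**Working it through.** **Inputs.** p1 = 0.96, p2 = 0.65, two-sided 5%, power 0.80, 21 per group, 20% attrition and 27 per group (all from Sample size); Fisher's exact test (Abstract; Statistical analysis); rejection when two-sided p < 0.05 (Statistical analysis).

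**1. Reproducing the protocol's 21.** With z(0.975) + z(0.80) = 2.8016, squared 7.849:
- Arcsine: h = 2·arcsin√0.96 − 2·arcsin√0.65 = 2.7389 − 1.8755 = 0.8634, so n = 2 × 7.849 / 0.8634² = 21.06. Approximate power at 21 is 79.9%.
- Unpooled normal: n = 7.849 × (0.96×0.04 + 0.65×0.35) / 0.31² = 7.849 × 0.2659 / 0.0961 = 21.7.
- Pooled normal: 24.4, so 25. With continuity correction: 30.5, so 31.
- Exact power of the uncorrected Pearson chi-square at 21 per group: 79.2%.

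So 21 is close to the uncorrected large-sample methods and far from the continuity-corrected one, which is the formula closest in spirit to Fisher's test.

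**2. Attrition.** 21 / 0.80 = 26.25, rounded up to 27; 2 × 27 = 54. This is correct.

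**3. Fisher's test at 21 per group.** Power is the sum, over all pairs of outcomes with Fisher p < 0.05, of Bin(x1; n, 0.96) × Bin(x2; n, 0.65). The main terms are:

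| Closures, experimental | Probability | Significant if control closures are at most | Probability | Product |
|---|---|---|---|---|
| 21 | 0.4243 | 16 | 0.9076 | 0.385 |
| 20 | 0.3713 | 14 | 0.6433 | 0.239 |
| 19 | 0.1547 | 12 | 0.2941 | 0.045 |
| 18 | 0.0408 | 11 | 0.1623 | 0.007 |
| 17 or fewer | | | | <0.001 |

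The total is 0.676.

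**4. Other sizes and tests, same enumeration (96% v 65%).**

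| Evaluable per group | Fisher | Boschloo | Pearson, uncorrected |
|---|---|---|---|
| 21 | 67.6% | 76.6% | 79.2% |
| 27 | 76.5% | 85.6% | 89.5% |
| 28 | 79.0% | | 89.6% |
| 29 | 81.2% | | 90.6% |

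Fisher's power is not monotone in n (78.1% at 26, 76.5% at 27), but no equal group size from 20 to 28 reaches 80%. With the protocol's attrition, 29 evaluable would mean 29 / 0.80 = 36.25, so 37 per group and 74 in total.

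**5. Where the power goes.** The maximum type I error of Fisher's test is 2.3% at 21 per group and 2.6% at 27, about half of the permitted 5%. For Boschloo's test it is 4.8% and 4.5%. For Pearson it is 5.6% and 5.7%, so part of Pearson's advantage comes from exceeding 5%.

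**6. Other readings of the test.** Doubling the one-sided Fisher p-value gives the same 67.6% and 76.5%. A one-sided 5% Fisher test gives 76.6% at 21, and the protocol specifies two-sided tests in any case.

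**7. Sensitivity assumption only.** At 90% v 65%, Fisher's power is 38% at 21 and 47% at 27. The 90% is not a planning value in the Sample size section. It appears in the Introduction, where "The healing rate can reach 90% and 96" per cent refers to refractory macular hole.

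**The case against.** Four points can be made for the protocol.

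- **The 21 is not a miscalculation.** This stands. The section does not say which method was used, common approximations land within a patient or so of 21, and the attrition step is right. A reader might infer an arithmetic error, but the document does not show one. That 21 came from a large-sample formula is itself an inference: strictly rounded up, 21.06 and 21.7 both give 22. The shortfall under Fisher's test does not depend on which formula was used.
- **The attrition margin may cover the gap.** It does not. With no losses at all, 27 per group gives 76.5%.
- **Fisher's test is valid.** This also stands. Type I error is controlled and the primary comparison is not compromised. Only the power statement is wrong. The shortfall runs from about 3.5 points (27 evaluable) to about 12 points (21 evaluable).
- **A less conservative test is a preference, not a correction.** Fair. Boschloo's test at 21 still falls short of 80%, and it exceeds 80% at 27 only without the planned attrition.

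A stronger reading is tempting: that even 68% is optimistic, because the Introduction describes 96% as a healing rate in refractory macular hole while the Sample size section uses it as a type I closure rate in this population. The documents do not support that conclusion. The cited sources are not at hand and may report type I closure. The 65% control rate is just as uncertain, and a lower true control rate would raise power. The protocol also says openly that no randomised trial of this procedure in this condition has been reported. The direction of any bias is therefore unknown.

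**Conclusion.** The point holds as a mismatch between the sizing method and the named analysis. On the protocol's own assumptions (96% v 65%, two-sided p<0.05, unstratified Fisher's exact test), power is 67.6% with 21 evaluable per group, not 80%. It is 76.5% if all 54 are evaluable, and 29 evaluable per group are needed to reach 80%. The chance of missing the planned effect at 21 per group is about one in three (32.4%) rather than one in five.

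The result takes the planning rates as true and equal numbers evaluable in each group. It does not show that those rates are too favourable, that the type I error is affected, or that a non-significant result would be misreported. Because the protocol itself names the test twice, this is not a detail left to an analysis plan that is not shown.

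**What to change.** **Required.** Keep 54 participants and correct the power statement in Sample size, along these lines:

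> With Fisher's exact test, two-sided at 5%, power to detect 96% v 65% is about 68% with 21 evaluable participants per group and about 76% with 27.

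This costs one sentence and no patients. The stated power becomes less favourable.

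**Optional.** Before the first patient is enrolled, prespecify a less conservative valid test for the primary outcome, such as Boschloo's unconditional exact test, and state its power: 77% at 21 per group and 86% at 27. The text should say that this is still below 80% at 21. The test needs software other than the SPSS and GraphPad Prism named in Statistical analysis. The Trial status section puts the study in its preparatory stage, so on the document's own account the choice can be made without sight of data. Made after results are seen, it would not be credible.

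**Optional.** Add power at 90% v 65% (Fisher: 38% at 21, 47% at 27), labelled as a sensitivity assumption. Note that the Introduction describes the 90% and 96% as healing rates in refractory macular hole.
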